#### **2.4.3 The effects of tai chi on mental health**

TC is widely regarded as a feasible activity to improve the functional ability and health of people with various health conditions such as the elderly, patients with chronic diseases, and children with intellectual disabilities (Zou et al., 2018). The characteristics of TC emphasize the slow and dynamic weight transfer (requires strong lower limbs), combined with physical awareness, breathing control, and mental concentration (Zou, 2017). Many studies have shown that TC exercises can effectively improve PF ( Nguyen, 2012; Kong et al. 2019). In the past two decades, TC training which purely emphasizes health has become more popular in elderly centers, communities, clinics, and hospitals.

TC is a PA that also incorporates meditation, social, and cognitive elements. It is becoming more and more popular and aroused a lot of interest (Wayne, 2014). It involves the orchestration of learning actions, which requires episodic memory, visuospatial skills and rapid information processing. In addition, TC also speeds up heart rate and breathing, which helps to build a larger network of connections between neurons, thereby enhancing brain perfusion. Previous studies have also shown that TC is a safe and effective activity that can improve the physical balance and emotional health of non-disabled elderly people (Del-Pino-Casado, 2016; Wang, 2010).

TC has been proven to be beneficial both physically and psychologically (Wang, 2004). This suggests that TC can help reduce depression and improve the sustainability of positive effects of metabolic syndrome and depression, which has important implications for the prevention and management of cardiovascular disease. In addition, three recent reviews suggest that TC may have some positive effects on

the mental health of patients with depression (Wang, 2014; Chi, 2010; Wang, 2010). In addition, TC can reduce the severity of anxiety, stress, depression and leg strength in central obese patients with depressive symptoms (Liu et al. 2015).

## **2.5 Summary**

Under the COVID-19 epidemic since 2019, young people, especially college students, have further reduced the willingness to go out and exercise (Xiang, 2020; Shen, 2021), in addition, changes in lifestyle and behavior, increased sedentary or lying-down time (Palermi, 2020) or decreased willingness to exercise can lead to changes in psychologically, physically and Comorbidity aspects.

TC as a good intervention, non-pharmacological intervention for maintaining and improving cognitive function, mental health, and PF, has been confirmed by various experiments. However, the comprehensive effect of TC intervention needs to be further proved in college students.

## CHAPTER III

### Research Methodology

#### 3.1 Study design overview

The design of this study will be a RCT with two parallel groups with a 1:1 allocation ratio, allocation concealment and assessor blinding. The design follows the Consolidated Standards of Reporting Trials (CONSORT) and the Standard Protocol Items Recommendations for Interventional Trials (SPIRIT).

Eligible participants will be collected according to the requirements of the experimental design. According to the cluster sampling method, a two-arm, parallel controlled trial, randomized was conducted. The participants who will receive primary prevention education of cognition, mental health, and physical fitness will be divided into two groups: the 12-week 24 Form TC exercise intervention group (45 min per session, three sessions per week) or control group.

Cognitive performance, including executive function, memory, and processing speed, will be assessed by using SCWT at baseline prior intervention 2-3 days and within 2-3 days after the 12-week intervention. In addition, before and after the 12th TC training session, all participants in the TC exercise group will be only assessed cognitive performance by using SCWT and HRV test.

Furthermore, both the function and structure of brain regions related to cognitive performance will be measured by using rs-EEG, and autonomic nerves in the nervous system will be measured by using HRV, and fitness health factors (power of lower limbs, body mass index, body composition, cardiopulmonary function, muscle strength, balance, flexibility) will be measured at baseline prior intervention 2-3 day and within 2-3 days after the 12-week intervention. In addition, mental health will also be assessed by using Depression Status Inventory and State-Trait Anxiety Inventory Version at baseline prior intervention 2-3 days and within 2-3 days after the 12-week intervention.

All data collection of the group assignments will be blinded. The flow diagram

for this study is presented in figure 3.

[figure not shown]

**Figure 3** Flow diagram of the study design.

Version number2.0 ; Dated 15thFeb. 2022

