### 3.2.2 Sample size, screening, and allocation

#### (1) Sample size estimation

Depending on the type of data or study design, there are multiple methods that can be used to calculate the sample size. If suppose that the sample sizes of the Version number2.0 ; Dated 15thFeb. 2022

two groups in this design are equal, and compare the means of the two groups, use the following formula to calculate the sample size equation:

$$n = (Z_{crit} + Z_{pow})^2 * 2 * \sigma^2 / d^2 \quad \text{or}$$

$$n = (Z_{crit} + Z_{pow})^2 * (SD_1 + SD_2)^2 / (M_1 - M_2)^2$$

Here, n represents the sample size of each group; assuming that the two groups of samples are the same,  $\sigma^2$  represents the variance of either group; D represents the smallest detectable value between the two sample means. Zcrit and Zpow respectively represent the significance level and the standard normal deviation of 1- $\beta$  power. The standard normal deviation is the realization of the standard normal random variable, For the two-sided test, the Zcrit value is 1.96 and the significance level is 5%. The Zpow is 0.84 at 80% power and 1.28 at 90% power (Wang & Ji, 2020).

To determine the sample size (Lu et al., 2016), data from our previous prospective study on college students show that TC training achieved significant improvement in cognitive performance (TC group:  $0.392 \pm 0.087$ ; Inactive Control group:  $0.475 \pm 0.097$ ) after the seven-week intervention when compared with subjects in the control group (Converse, 2020). Our estimation of sample size was based on the independent Compare 2 Means analysis between the two groups. Calculations were performed with WinPepi software (Abramson, 2011), one of a set of computer programs for epidemiologists. An overall sample size of 40 participants (20 participants per group) achieves an 80% power at the 0.05 significance level. Taking into account the drop-out rate for each group, we expect that a total sample size is 50 participants (25 participants per group).

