### **3.3.2 Test sequence**

Following informed consent.

In the 1st study, all participants in TC exercise group will be assessed before and after a 45-minutes TC training session in 4th week to determine the effects of single TC training session. Both pre-test2 and post-test1 will be in the following order: 1)SCWT, and 2) HRV test.

In the 2nd study, all participants in both TC exercise group and control group will be assessed before and after 12-weeks to evaluate the long-term effects of TC training session. Both pre-test1 and post-test2 will be in the following order: 1)DSI and STAI, 2) SCWT, 3)HRV test, 4)PF test and Body Scale, and 5)rs-EEG.

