### **3.4.3 Stroop color word test**

The SCWT consisted of two sessions: word recognition (WR); color recognition (CR), and used software Eprime 2.0 Professional (Psychology SoftwareTools, Inc., Pittsburgh, PA), which allows online recording and voice-key triggering of the participants' verbal responses, for presenting the stimuli and collecting the data.

In order to further reduce the non-specific interfering factors of the Stroop task, such as practice times, stimulus encoding, contextual factors, color name facility, operational tasks, the amount of SOA, the subject's age and mood, the proportion of words and non-words (Rezaei, M., 2019; Edwards, S. et al., 1996), The stimuli were four-color word names presented in Chinese word as 红(RED), 黄(YELLOW), 蓝(BLUE) and 绿(GREEN). SCWT will produce two types of situations. In the case of the same word color, the meaning of the word matches the color ink. For example, the word BLUE is presented in blue ink; when the word color is inconsistent, the meaning of the word conflicts with the color of the ink. , Such as the word BLUE in red ink (Zhu, 2020). Participants will be asked to choose any a key (f, j, r, u) based on the word presented in four colors: red, yellow, blue, or green. The four colors used the left index finger, the right index finger, the left middle finger, and the right middle finger, respectively. For example, if the word color is yellow, whatever the word, the correct response is to press the "j" key with the right index finger. The stimulus consisted of randomly matched colors and words (120 incongruent trials, 40 congruent trials). All stimuli were presented for 500 ms followed by fixation point (+) for 250ms and a

stimulus remained displayed on the screen for a maximal duration of 1000 ms, see figure 4. The conflict effect of the two groups before and after inhibitory control training was evaluated through response time and error rate in both the congruent and incongruent stimulus (Xu et al., 2021). All subjects are required to practice until the correct rate is higher than 60% before the formal test can be conducted.

[figure not shown]

**Figure 4** SCWT process

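### Only the Tai Chi arm sits two extra Stroop tests in week 4, so any retained practice gain on this primary outcome cannot be separated from a Tai Chi effect

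*Protocol*

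**What the plan says.** Protocol 3.1 places the single-session study within the intervention period and in one arm only: "before and after the 12th TC training session, all participants in the TC exercise group will be only assessed cognitive performance by using SCWT". The same sittings also include the heart rate variability recording. Section 3.3.2 gives the same timing: "all participants in TC exercise group will be assessed before and after a 45-minutes TC training session in 4th week". At three sessions a week the 12th session falls in week 4, so the two sections agree. These two sittings are called pre-test2 and post-test1. Section 3.3.2 has both arms assessed only at pre-test1 and post-test2, before and after the 12 weeks.

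Section 3.6 lists SCWT response time and error ratio among the primary outcomes, with six HRV indices and EEG power. It analyses them by a repeated-measures ANOVA with group (TC, control) and time (pre-test1, post-test2).

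On practice, section 3.4.3 introduces its stimulus design with "In order to further reduce the non-specific interfering factors of the Stroop task, such as practice times". It fixes 120 incongruent and 40 congruent trials per sitting, and requires practice to above 60% correct before the formal test. Section 3.2.2 (2) excludes people who already have experience of cognitive tasks.

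On blinding, section 3.1 describes "a RCT with two parallel groups with a 1:1 allocation ratio, allocation concealment and assessor blinding" and adds "All data collection of the group assignments will be blinded". Section 3.2.2 (3) names three assistants for testing. It does not say which of them test in week 4 or at post-test2.

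**The concern.** The extra test exposure coincides exactly with randomised group. If familiarity with the task persists to post-test2, the group-by-time term for SCWT contains a TC effect plus a practice effect, and no contrast in the data separates them. Leaving the week-4 scores out of the ANOVA does not help, because the exposure comes before post-test2. The protocol itself treats practice as an interfering factor and screens out task experience at entry, then creates such experience in one arm.

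Section 1.4 ranks the single-session question as a tertiary aim and the 12-week effect as the primary aim. The lower aim therefore puts the higher one at risk.

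A second, smaller issue is that anyone who runs the week-4 tests knows that those participants are in the TC arm.

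**Working it through.** **1. Exposure before post-test2** (3.1, 3.3.2, 3.4.3)

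- Formal trials per sitting: 120 + 40 = 160.
- TC: pre-test1, pre-test2, post-test1 = 3 sittings, 3 × 160 = 480 trials.
- Control: pre-test1 = 1 sitting, 160 trials.
- The ratio is 3:1. The pre-test practice runs are not counted.

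**2. The plan's own sample size** (3.2.2 (1))

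Inputs: TC 0.392 (SD 0.087), control 0.475 (SD 0.097), two-sided 5%, 80% power.

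- Difference: 0.475 − 0.392 = 0.083.
- Common SD: √[(0.087² + 0.097²)/2] = 0.0921.
- Standardised effect: 0.083/0.0921 = 0.90.
- n per group = (z₀.₉₇₅ + z₀.₈₀)² × (0.087² + 0.097²)/0.083² = 19.3, rounded up to 20.

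This reproduces the stated figure: "An overall sample size of 40 participants (20 participants per group) achieves an 80% power at the 0.05 significance level". The 25 per group enrolled equals 20/(1 − 0.20), an implied dropout of 20%. The sample size is not at fault here. The protocol labels these means only as cognitive performance, so applying their scale to SCWT is an assumption.

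**3. False-positive rate under a one-arm practice gain**

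Let g be the gain retained at post-test2 in the TC arm only, in SDs of the score, and ρ the pre-post correlation. The protocol gives neither, so both are assumed. In a two-group, two-time ANOVA the interaction test equals the two-sample t-test on change scores. With no TC effect and equal variances:

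- noncentrality = [g/√(2(1 − ρ))] × √(n/2), with 2n − 2 degrees of freedom;
- at ρ = 0.5 the first divisor is 1, so the result also applies to a comparison of post-test scores alone;
- example, n = 25, g = 0.2, ρ = 0.5: 0.2 × √12.5 = 0.71 on 48 df, which gives a rejection probability of 10.7%.

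| g (SD) | n = 25, ρ = 0.5 | n = 25, ρ = 0.7 | n = 20, ρ = 0.5 |
|---|---|---|---|
| 0 | 5.0% | 5.0% | 5.0% |
| 0.1 | 6.4% | 7.3% | 6.1% |
| 0.2 | 10.7% | 14.6% | 9.5% |
| 0.3 | 18.0% | 26.9% | 15.2% |
| 0.5 | 41.0% | 60.9% | 33.8% |

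For any non-zero g, a correlation below 0.5 gives lower rates than the ρ = 0.5 columns.

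**4. Gain against the planned effect**

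Subject to the scale caveat in step 2, a gain of 0.2 SD is 0.2/0.90 = 22% of the design effect, and 0.5 SD is 56%.

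**The case against.** The exposure count is not in dispute, but there are fair arguments about what follows from it.

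- **The gain may be small or nil.** About eight weeks pass between the 12th session and post-test2, and everyone practises to above 60% correct before the formal test. The first point stands: zero belongs in the range. The second helps little, because the rule sets a floor for accuracy. It neither matches later exposure nor addresses response time.
- **The direction is not guaranteed.** A reader might infer that the bias always favours TC. The protocol does not show this. Response time and error ratio need not move together, and repeated testing can bring boredom. The direction is conditional on practice improving performance.
- **Blinding.** A reader might infer that the testers are unblinded. The protocol states that they are blinded and does not say who tests when, so loss of blinding is a risk inferred from a single named team. SCWT is presented and recorded by computer, which leaves tester knowledge little route to the score. The fitness tests in 3.4.5, some timed or read by a tester, are more exposed.
- **HRV.** A reader might infer that HRV is affected in the same way, since its extra sittings are equally one-sided. Section 3.4.4 describes a passive 2.5-minute seated recording, and the protocol names practice as a problem for the Stroop task only. The documents do not support extending the practice argument to HRV.
- **Reach.** SCWT is one of several primary outcomes listed without ranking. EEG, fitness and the questionnaires are not taken in week 4 and carry no extra test exposure.

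**Conclusion.** The point holds for SCWT. Before post-test2 the TC arm has had three times the formal test exposure of the control arm, and the planned group-by-time comparison cannot separate retained practice from a TC effect. Analysis cannot repair this, because no control participant has the extra exposure and no TC participant lacks it by design.

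The size of the bias cannot be derived from the protocol. With 25 per group, a retained gain of 0 to 0.5 SD and a pre-post correlation of 0.5, the false-positive rate runs from the nominal 5% to 41%, and higher if the correlation is higher. These rates illustrate assumed gains; they are not estimates for this trial.

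The blinding issue is a secondary risk, mainly for tester-read fitness outcomes.

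**What to change.** Run the Study 1 pre/post SCWT and HRV pair around one TC session held after post-test2 is complete. Both arms then reach post-test2 with one prior SCWT sitting, and the testers have seen nothing specific to an arm through this sub-study. Sections 3.1 and 3.3.2 would need the new timing, and the test labels in 3.6 should follow.

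Cost: the tertiary acute effect is measured in participants trained for 12 weeks rather than four. One session is added, and it must fit the March to July 2022 data-collection window (3.2.2 (3)) and the limits that epidemic control places on group sessions (3.5.1).

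If week 4 must be kept, controls need the same paired tests at the same interval, about 25 extra visits. That would equalise practice and give Study 1 a concurrent comparator, but it would not by itself keep testers blind, because only one arm does TC between the two tests. Post-test2 should then be run by those of the existing assistants who did not run the week-4 tests, and the protocol should say so.

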## 3.2 Recruitment and sample

### 3.2.1 Recruitment

Study recruitment will be conducted on the campus of Huzhou University. Preliminary recruitment information and requirements will be posted on both the job flyer and university social pages, and interested potential participants can contact the principal investigator by calling the phone number provided or via email in the job flyer. In the first week before the formal experiment, the principal investigator will arrange a meeting for about an hour was arranged in the Sports Anatomy and Physiology Laboratory at 12 o'clock every day to clarify and explain the specific experimental process, and select eligible volunteers, which include taking PARQ and IPAQ questionnaires, and Control the inclusion and exclusion criteria, select eligible subjects and sign the informed consent form.

In addition, this study will use Stratified Blocked Randomization. An independent statistician will first stratify eligible subjects according to "gender" and "BMI ranges that are underweight (under 18.5 kg/m^2), normal weight (18.5 to 25kg/m^2), overweight (25 to 30kg/m^2), and obese (over 30kg/m^2)", block followed by randomization to TC or control group, ensuring that each subject will be randomly assigned to either intervention or control and there is a balance between the number and the BMI value of subjects in both groups. Finally, eligible volunteers will be randomly assigned to the TC group and the control group by envelope sampling. Of course, during any of the above processes or times, the volunteer can ask questions about the research project, and the researcher will further explain and answer the questions until the volunteer understands. Volunteers can still withdraw from the study at any time without affecting their rights during volunteers participating in this study.

### 3.2.2 Sample size, screening, and allocation

#### (1) Sample size estimation

Depending on the type of data or study design, there are multiple methods that can be used to calculate the sample size. If suppose that the sample sizes of the Version number2.0 ; Dated 15thFeb. 2022

two groups in this design are equal, and compare the means of the two groups, use the following formula to calculate the sample size equation:

$$n = (Z_{crit} + Z_{pow})^2 * 2 * \sigma^2 / d^2 \quad \text{or}$$

$$n = (Z_{crit} + Z_{pow})^2 * (SD_1 + SD_2)^2 / (M_1 - M_2)^2$$

Here, n represents the sample size of each group; assuming that the two groups of samples are the same,  $\sigma^2$  represents the variance of either group; D represents the smallest detectable value between the two sample means. Zcrit and Zpow respectively represent the significance level and the standard normal deviation of 1- $\beta$  power. The standard normal deviation is the realization of the standard normal random variable, For the two-sided test, the Zcrit value is 1.96 and the significance level is 5%. The Zpow is 0.84 at 80% power and 1.28 at 90% power (Wang & Ji, 2020).

To determine the sample size (Lu et al., 2016), data from our previous prospective study on college students show that TC training achieved significant improvement in cognitive performance (TC group:  $0.392 \pm 0.087$ ; Inactive Control group:  $0.475 \pm 0.097$ ) after the seven-week intervention when compared with subjects in the control group (Converse, 2020). Our estimation of sample size was based on the independent Compare 2 Means analysis between the two groups. Calculations were performed with WinPepi software (Abramson, 2011), one of a set of computer programs for epidemiologists. An overall sample size of 40 participants (20 participants per group) achieves an 80% power at the 0.05 significance level. Taking into account the drop-out rate for each group, we expect that a total sample size is 50 participants (25 participants per group).

## (2)The screening criteria

Inclusion criteria required that participants: 1) ages between 18 and 22 years, 2) could be independently ambulant, 3) were able to participate in a low-moderate intensity gentle movement group for 12 weeks, 4) attend classes on the Huzhou Version number2.0 ; Dated 15thFeb. 2022

University, 5) Normal vision or corrected vision, no color blindness, 6) being nonsmoker, not drinking alcohol, 7) not being physically active regularly (more than once per month), 8) not taking antioxidant supplementation, 9) no use of medication regularly, 10) absence of musculoskeletal pain or condition that limits exercise practice, and 11) the commitment of attending the TC sessions, and a self-reported sedentary lifestyle (i.e., not engaging in PA for the last 6 months).

Exclusion criteria included participants who: 1) participated in any type of professional sports, 2) reported any history of cardiopulmonary disease, 3) were able to participate in a low-moderate intensity gentle movement group for 12 weeks, 4) are pregnancies or suspect to be pregnant, 5) Take any prescription drugs (except oral contraceptives), take acute infections, illegal drugs, pregnancy, and vast physical exercise during the previous 2 weeks, 6) experienced in applying cognitive tasks or any limitations in the ability to complete cognitive testing procedures, 7) are with and without previous meditative movement and/or meditation practice, and 8) not allowed to consume any caffeinated or alcoholic products during the days of their study participation.

Potential participants will first complete a screening questionnaire, including International Physical Activity Questionnaire (IPAQ) and Physical Activity Readiness Questionnaire (PARQ), to determine their eligibility. IPAQ will be used to screen all participants for sedentary lifestyles (Tremblay et al., 2017), PARQ will be used to screen all participants for any serious health concerns that would preclude their involvement in PA (American College of Sports Medicine, 2018).

Eligible participants will receive information about this study and will have a discussion with researchers about the information provided. After signing the written informed consent, those interested in participating will arrange a baseline assessment of the results.

